### Statistical methods

#### Statistical analysis plan

We are currently collecting data from 41 of 48 child/adolescent ASD patients and their parents/guardians. Treatments will end during the spring of 2020, and analysis of the data will commence in the summer of 2020. The purpose of this study is to examine the relative efficacy of ACAT for child/adolescent ASD patients and their parents/guardians, in terms of ASD awareness scores, compared to the TAU group. Therefore, the primary analysis will evaluate the differences in score variations (i.e., the ACAT and TAU groups’ mean variations) for ASD awareness from week 0 (baseline) to week 6. Relative efficacy will be indicated when the point estimate of mean variation difference has a positive value and when the value of the ACAT group statistically exceeds that of the TAU group. The examination of scores will be based on an analysis of covariance (ANCOVA) for interval estimation of mean variation differences and calculation of the P value using allocation factors as adjustment factors (gender and AKQ-C score). The secondary evaluation of efficacy items will supplement the main results of the analysis, and redundancy will not be adjusted. The level of significance for the hypothesis test is 5% on two sides, with a two-sided confidence interval of 95%.

The results of the BACE-3, AKQ-P, SDQ, Vineland-2, DSRS-C, PREQ, and GHQ-12 (self-completed by parents) will be analyzed using the same techniques used for the assessment of the main evaluation items. In addition, EEG of individuals with HF-ASD as well as their parents/guardians will be recorded at pre-intervention, post-intervention, and follow-up to investigate neurological changes. EEG signals will be registered with a 19-channel box of Mitsar-EEG 201 (Mitsar Co. Ltd.). The 19-channel EEG cap will be fitted in accordance with a standard 10–20 system. EEG analysis will be conducted based on graph theory. The overall efficiency, clustering coefficients, connection between the left and right hemispheres, and network resilience will be calculated and compared between the ACAT and TAU groups.

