### Randomization and blinding

Enrollment and randomization are based on the central registration system of the Clinical Research Data Center at Chiba University Hospital, Chiba, Japan. Two allocation factors are used for stratification: the degree of knowledge (high or low) regarding the characteristics of ASD according to the primary outcome measure, the Autism Knowledge Quiz-Child (AKQ-C), and gender (male or female). At the end of the baseline assessment, eligible participants will be randomly assigned to either the TAU arm or ACAT plus TAU arm at a ratio of 1:1, with assignments made using the minimization method, ensuring a balance across baseline AKQ scores and gender. Each participant will then be assigned to one of the two treatments. Participants will not be blinded to the group to which they are assigned before consenting to participate in the study. However, trained testers, who will assess all outcome measures except the self-assessment scale, will be blinded to the group.

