### Outcome measures

#### Primary outcomes

##### Autism Knowledge Quiz-Child (AKQ-C)

AKQ-C [17] has two sections, namely, a five-item structured interview on “awareness of autistic characteristics” and a 15-item knowledge quiz. The main evaluation items of this study include variations in the “awareness of autistic characteristics” measured in section 1 of the AKQ-C, which will be administered during the pre-intervention, post-intervention, and follow-up period.

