### Sample size

The sample size was calculated using the G*power software version 3.1.9.2 with a power of 0.80 and *α* = 0.05 (two-tailed). In a previous study [17], the change in AKQ’s “ASD awareness” was 2.26, and the effect size was 0.92. Considering a drop out ratio of 20%, the ideal sample size was estimated as 48.

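### Read literally, the primary ANCOVA adjusts the awareness change for the high/low AKQ-C minimisation factor, not the continuous baseline awareness score: the test is valid but gives up some precision, and the covariate should be named

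*Protocol article*

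**What the plan says.** Three places in the protocol article bear on the covariate.

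- **Endpoint.** The AKQ-C has two sections: a five-item interview on awareness and a 15-item knowledge quiz. The main evaluation item is "variations in the “awareness of autistic characteristics” measured in section 1 of the AKQ-C". The primary comparison is the between-arm difference in mean change "for ASD awareness from week 0 (baseline) to week 6" (Statistical analysis plan).
- **Model.** The same section specifies an ANCOVA, with "calculation of the P value using allocation factors as adjustment factors (gender and AKQ-C score").
- **Allocation factor.** Randomization and blinding defines one of the two factors as "the degree of knowledge (high or low) regarding the characteristics of ASD according to the primary outcome measure", the AKQ-C; the other is gender. The same paragraph describes the aim of minimisation as "ensuring a balance across baseline AKQ scores and gender".

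No cut-off between high and low is given. The continuous week-0 section 1 score is not named as a covariate anywhere.

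**The concern.** A change score depends on its own baseline, since participants who start low have more room to rise. The usual remedy is to adjust for the baseline as measured. The model sentence instead points back to the allocation factors, and the AKQ-C allocation factor is defined as a dichotomy. Two categories remove only part of the baseline variation. What remains within them inflates the residual variance and lets chance differences in baseline awareness move the estimate.

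There is also a question of which score is meant. The factor is described as a degree of knowledge, while the endpoint is awareness (section 1), so the article does not settle whether the split was made on section 1, section 2 or the total. Several different primary models would comply with the text.

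At stake is the width of the confidence interval for the single primary comparison, with about 19 evaluable participants per arm after the planned 20% dropout.

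**Working it through.** **1. The plan's sample size.** Inputs from the Sample size section: "the change in AKQ’s “ASD awareness” was 2.26, and the effect size was 0.92"; "with a power of 0.80 and *α* = 0.05 (two-tailed"); dropout 20%; total 48. The implied SD is 2.26/0.92 = 2.46.

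- Normal approximation: n per arm = 2(1.960 + 0.842)²/0.92² = 18.6, so 19. Then 38/0.8 = 47.5, so 48.
- Exact t-test: 20 per arm (power 0.809; 19 per arm gives 0.788). Then 40 × 1.2 = 48, or 40/0.8 = 50.

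The stated 48 is reproduced, and it is an unadjusted two-sample calculation. At 24 × 0.8 = 19.2 per arm the unadjusted t-test has power 0.79.

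**2. Residual variance of the change.** The documents give neither the correlation r between baseline and week 6 nor the cut-off. Assumptions: equal SDs (set to 1), normal scores, median split, r from 0.3 to 0.7. Write B for baseline awareness. Then change = −(1 − r)B + error, with error variance 1 − r². Hence:

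- unadjusted: (1 − r²) + (1 − r)² = 2(1 − r)
- continuous baseline: 1 − r²
- high/low factor: (1 − r²) + (1 − r)²[1 − (2/π)c²]

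Here c is the correlation between baseline awareness and the score that was split; c = 1 if the split was on awareness itself. For r = 0.5 and c = 1: 0.75 + 0.25 × 0.363 = 0.841, against 0.750 for the continuous baseline.

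**3. Split on awareness (c = 1).** Power is from the noncentral t at 19.2 per arm, taking the effect as 0.92 SDs of the change.

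| r | high/low | continuous | variance ratio | SE larger by | power, high/low vs continuous |
|---|---|---|---|---|---|
| 0.3 | 1.088 | 0.910 | 1.196 | 9.3% | 0.88 vs 0.93 |
| 0.5 | 0.841 | 0.750 | 1.121 | 5.9% | 0.86 vs 0.89 |
| 0.7 | 0.543 | 0.510 | 1.064 | 3.2% | 0.83 vs 0.85 |

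The variance ratio gives the participants needed for equal precision: about 20%, 12% and 6% more.

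**4. Split on another AKQ-C score (c = 0.5, for illustration).** The SE is larger by 20.5%, 13.1% and 7.2% at r = 0.3, 0.5 and 0.7. Power is 0.82 vs 0.93, 0.81 vs 0.89 and 0.80 vs 0.85.

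**5. Simulation.** 38 completers, minimisation on high/low and gender, split on awareness, 3,000 runs per setting. With no effect, the mean high/low estimate was between −0.002 and 0.005 and type I error was 4.6% to 5.5%. Power, high/low vs continuous, was 0.87 vs 0.92, 0.85 vs 0.89 and 0.83 vs 0.85. The high/low estimate correlated −0.20 to −0.38 with the chance between-arm difference in baseline, whose SD was about 0.22. If a difference of that size lay wholly within categories, then at r = 0.5 it would move the estimate by 0.5 × 0.22 = 0.11, against an effect of 0.92.

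**The case against.** The strongest reply is that the article does not say the covariate is dichotomised. The parenthesis says score, the model is an ANCOVA, and the randomisation section also speaks of baseline AKQ scores. Using high/low for allocation and the score for analysis is compatible with the text. If the score is the continuous section 1 baseline, the criticism falls away. This stands: high/low is the literal reading, not an established fact.

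Four stronger inferences are tempting, and the documents do not support them.

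- **That the wrong section was used.** The factor is tied to the primary outcome measure, and knowledge is also part of the instrument's name. A worst case of 33% more participants (r = 0.5: 1.000/0.750) needs the split to carry no information at all about baseline awareness. That is extreme for two sections of one instrument.
- **That the estimate is biased.** Regression to the mean acts on both randomised arms alike. The simulation shows no systematic bias and a nominal error rate. Chance imbalance moves the result of one trial and is already counted in its standard error, so it is not a second harm on top of the lost precision.
- **That the trial is underpowered.** Power under the high/low model stays at about 0.80 or above in the scenarios of steps 3 and 4, because 48 was computed without covariates.
- **That the adjustment is improper.** Adjusting for minimisation factors is a standard, valid analysis.

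It may also be said that covariate coding belongs in the full protocol. But the article does state a primary model with its covariates, and the point is that a more precise one is available from data already collected.

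**Conclusion.** The concern holds in a limited form. Read with the randomisation section, the primary model adjusts the awareness change for a two-level factor and gender. The wording leaves open a continuous score, and the section of the AKQ-C is not stated. If the factor is entered as high/low, the loss is a standard error about 3% to 9% larger and power 2 to 5 points lower for r = 0.7 down to 0.3, more if another AKQ-C score was split. These figures rest on an assumed r, equal SDs and a median split, none of which the documents give. This is a modest, avoidable loss of precision together with an ambiguity in the primary covariate; it does not make the test invalid. It is worth correcting because the remedy is almost free.

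**What to change.** Before database lock, write the primary model as: week 0 to week 6 change in AKQ-C section 1 ~ arm + gender + continuous week-0 AKQ-C section 1 score. State which AKQ-C score defined the high/low minimisation factor and where it was cut. If it was cut from section 2 or the total, keep high/low as an additional term, so that the analysis still reflects the allocation.

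The cost is a sentence or two in the plan and at most one degree of freedom. No new data are needed, since section 1 is already collected before the intervention. The sample size stays at 48, because it was derived without covariate adjustment.

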**Methods:**

This multisite study is a randomized controlled trial. In total, 24 participants will be assigned to the ACAT group and 24 to the treatment-as-usual (TAU) group. The ACAT group will receive a weekly 100-min session for 6 weeks, regular medical care, and one follow-up session. In this ongoing clinical trial, we will compare the scores of the measures recorded in the pre- and post-intervention stages between the ACAT and TAU groups. A total of 41 patients out of a target of 48 have participated in the trial to date. The primary outcome measure is the Autism Knowledge Questionnaire. Secondary outcome measures include Barriers to Access to Care Evaluation 3rd Edition, the Strengths and Difficulties Questionnaire, the Vineland Adaptive Behavior Scales second edition, the Parenting Resilience Elements Questionnaire, the General Health Questionnaire 12, and the Depression Self-Rating Scale for Children assessments, as well as an electroencephalographic recording.

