##### Vineland Adaptive Behavior Scales second edition (Vineland-2)

Vineland-2 [38] is a semi-structured interview for parents to capture the developmental norm of adaptive behavior in individuals aged 0–92 years. Interviews will be conducted with parents/guardians about their children at three different time points: pre-intervention, post-intervention, and follow-up.

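### Read literally, the plan adjusts seven secondary scales for gender and AKQ-C but not for their own week-0 scores, which costs precision without biasing the comparison

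*Protocol article*

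**What the plan says.** The section Statistical analysis plan of the Protocol article defines the primary comparison as the difference between arms in mean change in ASD awareness from week 0 to week 6. It is estimated by ANCOVA, with "calculation of the P value using allocation factors as adjustment factors (gender and AKQ-C score") as the stated covariates. These two are the minimization factors listed under Randomization and blinding.

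The same section then takes BACE-3, AKQ-P, SDQ, Vineland-2, DSRS-C, PREQ and GHQ-12 together and says that they "will be analyzed using the same techniques used for the assessment of the main evaluation items". No covariate list specific to any of these scales appears in the article.

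Under Secondary outcomes, every one of the seven is measured before the intervention. For Vineland-2, for example: "Interviews will be conducted with parents/guardians about their children at three different time points: pre-intervention, post-intervention, and follow-up".

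EEG is also listed as a secondary outcome, but it has its own graph-theory analysis, for which no change score or covariates are stated.

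**The concern.** For the primary outcome, the AKQ-C score is both an allocation factor and a baseline measure on the outcome's own instrument. That second role disappears when the model is carried to other scales. AKQ-C is a child's score on autism awareness and knowledge. It is not the baseline of parental GHQ-12, child DSRS-C or Vineland-2, nor of AKQ-P, which is the separate parent version. A change-score model without the scale's own baseline fixes the slope of week 6 on week 0 at 1, whatever the data show. ANCOVA on the own baseline estimates that slope.

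Minimization balances only AKQ-C level and gender, so the design does nothing to limit chance imbalance on the other scales. About 19 to 20 evaluable participants per arm are expected, so the choice of covariate affects how much these comparisons can show. The Discussion attaches its expectations on social adaptation, self-stigma, depressive symptoms, parental mental health and parenting resilience to these scales.

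**Working it through.** **Inputs**

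- From Sample size: power 0.80, two-sided 5%, the awareness change "was 2.26, and the effect size was 0.92", dropout 20%, total 48. From the abstract: 24 per arm.
- From Statistical analysis plan: outcome is the week 0 to week 6 change; covariates are gender and AKQ-C.
- Assumed, because the article does not give them: ρ, the correlation between a scale's week-0 and week-6 scores, taken from 0.3 to 0.9; r, the correlation between baseline AKQ-C and the scale's own baseline, taken as 0 and 0.5; and equal SDs at both visits, set to 1.

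**Step 1: the plan's own figure.** Normal approximation: n per arm = 2 × (1.96 + 0.84)² / 0.92² ≈ 18.5, so 19 per arm and 38 in total; 38 / 0.8 = 47.5, rounded up to 48. The two-sample t-test gives 19.55, so 20 per arm and 40 in total; 40 / 0.8 = 50, or 40 × 1.2 = 48. The stated 48 reproduces. Evaluable number: 24 × 0.8 = 19.2 per arm. The steps below use 20.

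**Step 2: variance with and without the own baseline.**

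- Change score, own baseline not in the model, r = 0: residual variance 2(1 − ρ).
- ANCOVA on the own baseline: residual variance 1 − ρ².
- Ratio: 2(1 − ρ) / [(1 − ρ)(1 + ρ)] = 2/(1 + ρ).
- If AKQ-C correlates r with the scale's baseline: ratio = [(1 − ρ)²(1 − r²) + (1 − ρ²)] / (1 − ρ²).

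The simulated column has 20 per arm, r = 0, with gender and AKQ-C in both models. The last column gives the power of the literal model, with r = 0 and 20 per arm, at the effect for which the own-baseline model has 80%.

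| ρ | Ratio, r = 0 | Ratio, r = 0.5 | Simulated, r = 0 | Power of literal model |
|---|---|---|---|---|
| 0.3 | 1.54 | 1.40 | 1.52 | 62% |
| 0.5 | 1.33 | 1.25 | 1.29 | 68% |
| 0.7 | 1.18 | 1.13 | 1.16 | 73% |
| 0.8 | 1.11 | 1.08 | 1.06 | 76% |
| 0.9 | 1.05 | 1.04 | 1.03 | 78% |

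**Step 3: the same loss seen through baseline imbalance.** Given a chance baseline difference D between arms, the literal model's estimate is shifted by −(1 − ρ)D (r = 0). One standard error of D is √(2/24) = 0.29 SD with 24 per arm and √(2/20) = 0.32 SD with 20. The shift from an imbalance of that size is:

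- ρ = 0.5: 0.14 to 0.16 SD
- ρ = 0.7: 0.09 SD
- ρ = 0.9: 0.03 SD

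The simulated slopes on D were −0.71, −0.49, −0.32, −0.19 and −0.10 for ρ from 0.3 to 0.9, and about 0 once the own baseline was added. With r = 0.5 and ρ = 0.5 the slope was still −0.37, so AKQ-C removes only part of the shift.

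**Step 4: one quantity, not two.** (1 − ρ)² + (1 − ρ²) = 2(1 − ρ). At ρ = 0.5 this is 0.25 + 0.75 = 1.00, and 1.00 / 0.75 = 1.33. The imbalance term is exactly the excess variance of Step 2, so it must not be counted as a second harm.

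**The case against.** The strongest reply is that using the same technique need not mean using the same covariates. In the primary model AKQ-C acts as a baseline, so by analogy the authors may intend each scale's own baseline to take its place. Nothing in the article rules that out, and the article condenses a fuller protocol. This stands as a limit on certainty: the finding rests on the literal reading. It does not remove the point. The article does fix a covariate set, describes it as the allocation factors, and applies it to seven scales without qualification. Under either reading the text needs the same sentence.

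A reader might go further in four ways that the documents do not support.

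- That every secondary outcome is affected. EEG is not; it is analysed separately.
- That the estimates are biased. The shift in Step 3 is conditional on the observed imbalance and averages to zero over randomizations. At ρ = 0.5 with 20 per arm, a one-standard-error imbalance moves the estimate by 0.16 SD against a standard error of √(2 × 0.5 × 2/20) = 0.32 SD, and the confidence interval already carries that variability.
- That AKQ-C is worthless as a covariate. The article gives no correlations. AKQ-P is the parent version of the same instrument and PREQ contains a knowledge factor, so some correlation is plausible, and it reduces the loss.
- That the trial's main conclusion is at risk. The plan calls the secondary analyses supplementary and sizes the trial on awareness alone.

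**Conclusion.** The point holds as an efficiency loss in the seven named scales, on the literal reading of the plan. With AKQ-C unrelated to the scale, the treatment-effect variance is 5% to 54% larger than with own-baseline ANCOVA over assumed ρ of 0.9 to 0.3. With r = 0.5 the range is 4% to 40%. The loss is material for ρ of about 0.3 to 0.7 and small at 0.8 or above. Its size rests on ρ, r and equal SDs at the two visits, none of which the article gives.

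It is not a validity error, and it leaves the primary analysis, the efficacy criterion and the total of 48 untouched. It is worth correcting because the better covariate is already collected and the correction costs almost nothing.

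**What to change.** Replace the cross-reference to the primary technique with an explicit model: for each of BACE-3, AKQ-P, SDQ, Vineland-2, DSRS-C, PREQ and GHQ-12, an ANCOVA with that scale's own continuous week-0 score, gender and the AKQ-C allocation factor as covariates. The change score can stay as the outcome, because once the own baseline is in the model the treatment estimate is the same as for the week-6 score.

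The cost is one sentence in the plan and one degree of freedom per model. No new data are needed, and neither the primary analysis nor the sample size changes. The covariates should be fixed before the secondary results are compared between arms.

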## Discussion

Children diagnosed with autism are typically portrayed as being significantly different from other children. The experiences of children diagnosed with autism are defined as either positive or negative [42]. Conversely, it has been reported that being diagnosed with ASD in the absence of aftercare avenues, including psychoeducation and assistance in increasing self-understanding, diminishes the benefit of a diagnosis [13, 17]. A diagnosis should deepen one’s understanding of ASD characteristics, and psychoeducation for ASD is crucial to continued understanding and awareness. This must follow a diagnosis to prevent the amplification of related psychological problems such as the perception of self-stigma and lowered self-esteem.

We expect that participants and parents assigned to the ACAT group who experience ACAT will gain a significantly greater understanding of ASD compared to those of the TAU group. Along with an enhanced comprehension of ASD, participants in the ACAT group are also expected to display improved social adaptation, decreased perception of self-stigma, and a reduction in depressive symptoms. Furthermore, the parents of participants are expected to experience less self-stigma, improved mental health, and reinforcement of nurturing resilience. A better understanding of a participant’s ASD characteristics may lead to improved mental health in parents and encourage adaptive behaviors in the participants. Importantly, Gordon et al. [17] reported no significant changes in participants’ self-esteem as a result of an enhanced understanding of ASD. This study assumes that improved self-esteem is experienced after increased social adaptation. However, there was no significant improvement in self-esteem in their study. ACAT may help to increase social adaptation through psychoeducation combined with CBT. We hope that the results of this study will support the benefits of a HF-ASD diagnosis in Japan. Some limitations should be noted, however. First, the comparative effectiveness of the psychoeducation phases of the PEGASUS and ACAT programs is unclear because of the differences in their components. This study is not designed to compare the psychoeducation phases of PEGASUS and ACAT. Hence, we cannot disentangle the specific effects of the psychoeducation phase used in the ACAT program. Second, ACAT is designed as family CBT, and our study design does not include individual CBT as a control group. Individual CBT dealing with problems related to autistic traits may be as effective as ACAT; nevertheless, it is expected that ACAT will be more acceptable and effective for younger participants. Further studies are warranted to establish the effectiveness of these treatment methods.

In conclusion, we expect that participants in the ACAT group will experience significantly increased self-awareness and understanding of ASD symptoms compared to those in the TAU group. We also expect the ACAT group to experience significantly improved social adaptation and mental health if the children and parents in this group gain an adaptive comprehension of their own autistic traits during the sessions. This intervention may contribute to the establishment of an effective treatment strategy based on the evidence gleaned from adolescents with ASD.

